## Methods

### Study design

The research will adopt a fully randomized-controlled 2 (mental simulation: mental simulation vs. control irrelevant visualization exercise) × 2 (self-control training: challenging Stroop task vs. easy Stroop task) between-participants factorial design. Mental simulation and self-control training manipulations will be the independent variables while self-reported alcohol consumption collected four-weeks after the initiation of the intervention will be the primary dependent variable. Baseline alcohol consumption and trait self-control will be included as covariates. Participants will be randomly allocated to one of the four intervention conditions according to a schedule generated by an online experimental randomising tool [102]. A participant flow diagram and overview of study design is provided in Figure 1. The study protocol has been submitted to, reviewed, and approved by Curtin University Human Research Ethics Committee.

**Figure 1 Fig1:**
[figure not shown]
**Trial Flowchart.** The diagram illustrates the flow of participants through the proposed intervention.

### Participants

Participants will be undergraduate students from a large University in Western Australia. Students will be eligible to participate if that are 18 years or older and non-abstinent with respect to alcohol consumption to be eligible to participate in the study. Participants will be excluded if they are heavy or dependent drinkers as identified by the Fast Alcohol Screening Test (FAST) [103]. Participants will be recruited using email circular and notice board advertisements distributed throughout the University and from a dedicated participant pool for undergraduate psychology students incentivised by course credit or a prize draw for shopping vouchers. The study is described as an intervention to reduce alcohol consumption. Assuming a medium effect size for mental simulation interventions on behavior reported by Pham and Taylor [31] (*d* = 0.56) and an effect size of similar magnitude for the effects of self-control resource training reported in Hagger et al.’s [81] meta-analysis (*d* = .62), a power analysis using G*Power v3.1 [104] setting power at .80 and alpha at .05, estimates that we will require a total sample size of between 120 and 144 participants with between 30 and 36 participants in each intervention group. The variation in the sample size estimate is due to the use of the two different effect sizes to compute the power analysis, each of which gives a slightly different result.

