Data on the primary dependent variable of alcohol consumption will be analysed using a 2 (mental simulation: mental simulation vs. no mental simulation) × 2 (self-control training: challenging vs. easy) factorial between-participants analysis of covariance (ANCOVA) with alcohol consumption at follow-up as the dependent variable and baseline alcohol consumption and trait self-control as covariates. The analysis permits the main and interactive effects of mental simulation and self-control training intervention components. We predict statistically-significant main effects of medium size of mental simulation and self-control training on alcohol consumption, but also expect a statistically-significant, medium-sized interaction effect such that participants receiving the mental simulation and challenging self-control training components will report significantly lower levels of alcohol consumption than participants receiving either of the intervention components alone and participants that received neither manipulation.

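### The required total is given as a range, one end per effect size, although both effects are tested in one sample; by the plan's own calculation 144 is the requirement

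*Protocol article*

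**What the plan says.** The Participants section of the protocol article assumes d = 0.56 for mental simulation and d = .62 for self-control training. It runs G*Power "setting power at .80 and alpha at .05" and reports that "we will require a total sample size of between 120 and 144 participants", "with between 30 and 36 participants in each intervention group". It gives one reason for the spread: "The variation in the sample size estimate is due to the use of the two different effect sizes to compute the power analysis". It names neither the test family nor the degrees of freedom, and it commits to no single number.

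The Study design section describes a single 2 × 2 sample: "Participants will be randomly allocated to one of the four intervention conditions". The Data analysis section fits one 2 × 2 ANCOVA, "with alcohol consumption at follow-up as the dependent variable and baseline alcohol consumption and trait self-control as covariates", and expects both components to show an effect: "We predict statistically-significant main effects of medium size of mental simulation and self-control training on alcohol consumption".

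**The concern.** Each end of the range answers a different question: 144 belongs to the smaller effect and 120 to the larger. If the two effects were studied in separate trials, each could have its own total. Here every participant contributes to both comparisons, so the requirement is the larger of the two totals. Treating any number from 120 to 144 as sufficient is a slip of logic, whichever test produced the figures.

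At stake is the meaning of the stated .80. A trial that stops at 120 complies with the text, yet on the calculation that the text reports it does not reach .80 for mental simulation. The text also does not say which size the trial is aiming for.

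**Working it through.** **Inputs**
- From Participants: d = 0.56 and d = .62, power .80, alpha .05, stated total 120 to 144, stated cell size 30 to 36.
- From Study design and Data analysis: four cells, two covariates, each main effect a comparison of N/2 with N/2.
- Inferred, not stated: f = d/2 (the conversion for a balanced two-level factor) and the degrees of freedom of the test.

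**Formula.** Noncentral F with noncentrality λ = f² × N, numerator df 1, 2 or 3, denominator df N − 4. Power is the probability that this F exceeds the central 5% critical value.
- d = 0.56: f = 0.28, f² = 0.0784
- d = .62: f = 0.31, f² = 0.0961

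**Step 1: reproduce the stated range.** Smallest N with power of at least .80, with the total rounded up to equal cells in brackets where it differs:

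| Test tried | d = 0.56 | d = .62 |
|---|---|---|
| F, 3 df (omnibus over four groups) | 144 | 118 (120) |
| F, 2 df | 126 (128) | 104 |
| F, 1 df (a main effect) | 103 (104) | 84 |
| Two means, normal approximation, two-sided | 102 | 82 |
| Two means, normal approximation, one-sided | 80 | 66 |

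Only the 3-df test returns both 144 and 120. Removing two further denominator df for the covariates does not change those two totals.

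**Step 2: power at each end on that 3-df calculation.**
- d = 0.56, N = 120: λ = 0.0784 × 120 = 9.41, power .716
- d = 0.56, N = 144: λ = 0.0784 × 144 = 11.29, power .803
- d = .62, N = 120: λ = 0.0961 × 120 = 11.53, power .810
- d = .62, N = 144: λ = 0.0961 × 144 = 13.84, power .883

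The only total in the range that gives .80 for both effects is its upper end.

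**Step 3: power on the planned 1-df main-effect tests.** λ is unchanged; only the degrees of freedom differ.

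| N analysed | d = 0.56 | d = .62 |
|---|---|---|
| 120 | .860 | .920 |
| 144 | .916 | .959 |

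For .80 these tests need 103 and 84 analysed participants.

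**Step 4: room for loss to follow-up on the 1-df test for d = 0.56.**
- Enrolling 120: 1 − 103/120 = 14%
- Enrolling 144: 1 − 103/144 = 28%

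**Illustrations only.** Treating the two tests as independent, the chance that both main effects are significant is .860 × .920 = .79 at 120 and .916 × .959 = .88 at 144. With an assumed 20% loss from 120 (96 analysed), 1-df power for d = 0.56 is .77. The article gives no loss figure and does not define .80 as the chance of detecting both effects.

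**The case against.** The strongest objection is that the shortfall at 120 arises only on a test that the article does not name and does not plan to use. The 3-df omnibus basis is inferred from the match at both ends. On the planned 1-df tests, 120 is more than enough for either main effect. The power figures also take no credit for the variance that the covariates explain. If d is on the unadjusted scale (the article does not say) and the covariates have a combined correlation R with the outcome (an assumption), λ is divided by 1 − R². At N = 120 and d = 0.56, 1-df power then rises from .86 (R = 0) to .89 (R = .3) and .94 (R = .5). At R = .5 even the 3-df figure reaches .84. All of this stands, and it rules out calling the trial underpowered at 120 with complete data.

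Two other strong readings fail. A reader might infer that an open range permits results-driven stopping and so inflates the type I error. The article describes no look at the results at 120, and its Procedure section keeps the experimenter blind to the mental simulation condition until the end of the study. A reader might also infer that 120 fails because the chance of detecting both effects is .79. That is not the stated criterion, and .79 is in any case close to .80.

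It can also be said that a journal article condenses, and that a fixed target may sit in the full protocol. But the point here concerns what the article does state: a range offered as the requirement, with the reason for it. The objection limits the consequence and leaves the logic untouched.

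**Conclusion.** The point holds in a limited form. Both effects are tested in one sample, so the requirement on the plan's own calculation is 144, and 120 supports .80 only for d = .62. On the calculation that reproduces the range, power for d = 0.56 at 120 is .72, about 8 percentage points below the stated level. That size rests on two inferences, the 3-df test and f = d/2, both drawn from the match at the two ends.

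The tempting stronger conclusion, that a trial of 120 is underpowered for mental simulation, is not supported. On the planned 1-df tests, 120 complete cases give about .86 and .92 before covariate gain or loss to follow-up. The practical gain from 144 is therefore modest: about .92 instead of .86 for the d = 0.56 main effect, and tolerance of 28% loss instead of 14%. The article should be corrected, but the design is not invalidated.

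**What to change.** Replace the range in Participants with one enrolment target of 144 (36 per cell), and name the test and degrees of freedom that were powered. If the authors prefer 120, they should keep it as the single target and restate the power for each effect on the named test: about .86 and .92 if that is the 1-df ANCOVA main effect, or .72 and .81 if it is the four-group omnibus test.

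Either option takes a sentence or two. The first costs at most 144 − 120 = 24 participants above the lower end and none beyond the total already stated. The second adds no participants.

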### Procedure

On recruitment, participants will be required to attend an initial laboratory session with the experimenter at a mutually agreed time. Participants will be provided with an information sheet outlining their expectations and given the opportunity to ask questions about study requirements prior to completing and signing a consent form. They will then be asked to complete a brief demographic questionnaire and baseline self-report measures of alcohol consumption and psychological mediator variables. Next, participants will be given an envelope corresponding to the condition to which they have been allocated that contains instructions for the mental simulation or control manipulations. The envelopes will be prepared by an independent researcher using coded labels to represent the mental simulation manipulation and control irrelevant visualization task so that the experimenter will be blind to the intervention conditions until the end of the study. All participants will be presented with a written script with a generic introduction section providing a brief rationale for changing their alcohol behavior. The instructions will inform participants that the purpose of the study is to keep their alcohol consumption within nationally-recognized ‘safe’ guideline limits to promote better health and reduce adverse effects. A definition of NHMRC guideline limit for alcohol consumption of 14 standard drinks per week, a definition of a standard drink, and examples of volumes and measures of typical drinks that constitute a standard drink will be provided. This will be followed by instructions for the mental simulation or control irrelevant visualization exercise according to the randomly-allocated trial condition (see Additional file 1).

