We will administer outcome measures of two forms of alcohol consumption in the current research: total alcohol consumption and frequency of ‘binge’ drinking. Our primary outcome variable in the current research is overall self-reported alcohol consumption by undergraduate students. We cannot expect students to curb their alcohol drinking altogether, so the target outcome identified for participants in the current study will be keeping alcohol consumption within the guideline limits specified by the Australia National Health and Medical Research Council (NHMRC). The NHMRC guideline limits on safe alcohol consumption are 14 standard drinks (each standard drink is equivalent to 12.5 ml of pure alcohol) per week. The guideline limits will be clearly outlined to participants in advance of the research commencing and our purpose was to ensure that students did not exceed this limit as it is associated with long-term (chronic) harm [4]. We do, however, recognise that the guidelines reflect limits aimed at reducing chronic harm and that other patterns of alcohol consumption prevalent in students may also present a serious threat to health. For example, the consumption of 14 standard drinks on a single occasion, once per week may mean that an individual’s consumption falls within NHMRC overall guideline limits, but would constitute increased risk of acute harm. High-risk single-session alcohol consumption, also known as ‘binge’ drinking, defined as consuming more than 4 standard drinks on a single drinking occasion by the NHMRC [4], is related to substantially increased health risks such as unintentional injury, increased probability of unplanned and unprotected sexual intercourse, and risk of being involved in violence and social disorder [9,99,100]. Given that students are more likely to engage in binge drinking than their non-student peers [10,101], binge drinking is considered an important risk factor for alcohol-related harm specific to this population. We will, therefore, include a secondary outcome variable, frequency of occasions of binge drinking, self-reported by participants to account for this risky pattern of alcohol consumption that is likely to be endemic in this population. The variable is defined as the number of single occasions in which an individual’s alcohol consumption exceeded 4 standard drinks [4].

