### Primary and secondary outcome measures

Our primary outcome measure is participants’ self-reported alcohol consumption over the previous four weeks consistent with NHMRC guidelines [4]. Our secondary dependent variable is participants’ self-reported number of binge drinking occasions over the previous four weeks. Both primary and secondary outcome measures will administered at baseline and at follow-up. Participants will be asked to recall and report the absolute number of standard drinks they had consumed and the number of occasions when they engaged in binge drinking, that is, exceeding more than 4 standard drinks on a single drinking occasion, per week over the previous four weeks [34,105]. The self-report measures are based on the time-line follow back technique which has been shown to provide precise estimates of alcohol drinking [106]. This measure uses a number of techniques to aid recall such as linking alcohol drinking with significant events. In addition, the FAST will be administered to students recruited to the study at baseline [103]. The measure comprises four items (e.g. “How often during the last year have you failed to do what was normally expected of you because of drinking?”) and has demonstrated adequate validity and reliability to assess the extent of heavy and dependent drinking. FAST scores will be used as a means to screen participants for heavy alcohol consumption that is indicative of alcohol dependency. Participants identified as heavy or dependent drinkers will be excluded from the study prior to engaging in the protocol. Participants identified as heavy or dependent drinkers by the FAST will be provided with a leaflet providing advice on how to seek professional help for their alcohol consumption.

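### The only standard-drink definition the article describes comes after the baseline alcohol report and before follow-up, so the reporting unit can shift between the two measurements

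*Protocol article*

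**What the plan says.** The Procedure section of the protocol article sets the order of the first session. After consent, "They will then be asked to complete a brief demographic questionnaire and baseline self-report measures of alcohol consumption and psychological mediator variables". Then: "Next, participants will be given an envelope corresponding to the condition to which they have been allocated". On the envelope's contents: "All participants will be presented with a written script with a generic introduction section". Still describing that script, the section gives the weekly guideline limit and says that "a definition of a standard drink, and examples of volumes and measures of typical drinks that constitute a standard drink will be provided".

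Under Primary and secondary outcome measures, the primary item asks participants to "recall and report the absolute number of standard drinks they had consumed" over the previous four weeks. The secondary item counts occasions above 4 standard drinks. Both are given at baseline and at follow-up. The Self-control training section describes the follow-up measures as identical to those at baseline.

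The current research defines a standard drink as 12.5 ml of pure alcohol and also says: "The guideline limits will be clearly outlined to participants in advance of the research commencing".

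Under Data analysis, follow-up consumption is the dependent variable of the 2 × 2 ANCOVA, with baseline consumption and trait self-control as covariates.

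**The concern.** A standard drink is a technical unit. A respondent who has not been shown the conversion may count glasses, cans or bottles. On the order described, the baseline count is given before the described teaching and the follow-up count after it. Identical items do not help if respondents learn the unit in between. The recall aids in the outcome section, such as linking drinking to events, help memory and do not calibrate the unit.

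Two things are at stake:

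- **Precision.** If people differ in how far their own count is from standard drinks, the baseline covariate carries extra noise and explains less of the follow-up variance.
- **Before-after statements.** The Background speaks of a significant reduction in both outcomes, and The current research of the greatest reduction in the combined group. If respondents move from servings to standard drinks, follow-up reports rise relative to baseline with no change in drinking, so a real reduction within a group could be masked.

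**Working it through.** **The plan's own figure.** The article gives no figure on this point. Its one computed figure, a total of 120 to 144, reproduces as a four-group omnibus F test with f = d/2, alpha 0.05 and power 0.80. For f = 0.28 the total is 144; for f = 0.31 it is 118, or 120 when balanced. The point does not depend on it; 144 is used below only as a base.

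**Size of a unit shift for one person (assumed servings).** Standard drinks = volume in ml × alcohol fraction / 12.5.

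- Wine: 150 × 0.13 / 12.5 = 19.5 / 12.5 = 1.56.
- Beer: 425 × 0.048 / 12.5 = 20.4 / 12.5 = 1.63.
- Nine such wines a week: 9 counted as glasses, 9 × 1.56 = 14.0 in standard drinks.
- Three on one occasion: 3 (no binge) as glasses, 3 × 1.56 = 4.7 (binge) in standard drinks.

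These only illustrate the mechanism. They do not estimate the trial effect.

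**Loss in the covariate (assumed inputs).** Take baseline and follow-up drinking as lognormal with log SD s = 0.7 and log-scale correlation 0.7. Baseline is divided by a lognormal personal conversion factor with coefficient of variation c; follow-up is in true units. The mean factor (say 1.5) cancels, so only variation between people matters.

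- Without a shift: r0 = (e^(0.7 × 0.49) − 1) / (e^0.49 − 1) = 0.4092 / 0.6323 = 0.647.
- With a shift: r1 = 0.4092 / √[0.6323 × (1.6323 × (1 + c²) − 1)].
- Residual variance ratio = (1 − r1²) / (1 − r0²).

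| c | r1 | ratio | 144 / ratio |
|---|---|---|---|
| 0.2 | 0.616 | 1.07 | 135 |
| 0.3 | 0.583 | 1.14 | 127 |
| 0.4 | 0.544 | 1.21 | 119 |

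The last column is the number of participants, with a clean covariate, that would give the same precision as 144 with the shifted one.

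**Bias check by simulation (assumed inputs).** 36 per cell; mean 40 and SD 20 drinks per four weeks, truncated at zero; correlation 0.6; baseline reports at a median 75% of true units with a person-level log SD of 0.25; follow-up in true units in every cell; 4,000 replicates; baseline drinking as the only covariate.

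- No true effect: type I error 0.052 with the shift and 0.052 without it.
- True effect of 0.35 SD: mean estimate −6.71 with the shift and −6.74 without it.
- Power for that effect: 0.66 with the shift and 0.73 without it.

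The estimate is in effect unchanged and the loss is in precision. The simulation examined a main effect. The same reasoning covers the interaction, because a shift common to all randomised cells is unrelated to allocation.

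If instead the personal miscount stays at both times, the estimate shrinks to −5.16 and power is 0.68. So dropping the teaching would not be a remedy; it belongs before both measurements.

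**The case against.** The strongest reply is that the article does not show the baseline form. Form wording is commonly left to the full protocol, and the form or the information sheet may already define the unit. The sentence in The current research about outlining limits beforehand points that way, and so do the mediator items on safe limits, which are also given at baseline. This stands in part: it is not established that participants do not know the unit at baseline, and the point must be conditional. It does not dispose of the point. The early sentence concerns the limits; the definition and volume examples are placed only in the script. The limits could be given beforehand and repeated later, but the article does not say so.

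A second reply is that no change score or within-group test of drinking is planned. The residualised change scores under Data analysis are for the psychological mediators. This also stands: the harm to before-after statements concerns description and wording, and the primary test is unaffected.

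A reader might go further and infer that the mental simulation group, having rehearsed and written about its own drinking, converts units more fully at follow-up, so that its reported drinking is inflated and the trial is biased against the intervention. In the same simulation, if the control arm took up only half of the correction, there would be a spurious difference of 4.5 drinks and a type I error of 0.40. Nothing in the article supports that case. Every participant reads the same introduction, and the control exercise is designed to carry an equivalent information load. A reader might also conclude that change from baseline is uninterpretable. That is too strong; it would be confounded with unit learning to an unknown degree.

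**Conclusion.** The point holds in a limited form. On the described order, the only unit teaching sits between the two measurements of outcomes counted in that unit, and the two sections on timing need reconciling. A common shift does not bias the planned main effects or interaction. It can raise the ANCOVA residual variance by about 7-21% and can confound any description of drinking or binge occasions as lower than at baseline.

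The percentages rest on assumed values: a lognormal distribution with log SD 0.7, a log-scale correlation of 0.7, conversion-factor variation of 20-40%, no conversion by anyone at baseline and full conversion by everyone at follow-up. The last pair is an extreme, so partial knowledge at baseline would give a smaller loss. If the baseline form already carries the definition and examples, only the clarification of timing remains.

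**What to change.** Place the same standard-drink definition and volume examples at the head of the alcohol items, before the first item, at both baseline and follow-up, with identical wording in all four groups. Keep the guideline rationale in the script after baseline. Reconcile The current research with Procedure on when the limits and the unit are explained.

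The material already exists, so the cost is moving a page and repeating it with the follow-up items. No extra visit, staff or participants are needed. The small downside is slightly more alcohol information before baseline, equal in all groups. The change must be made before baseline data are collected, because those reports cannot be recalibrated later. If they have already been collected without a definition, the report should avoid reading the before-after difference as a change in drinking.
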